### Data protection process

In order to ensure safety of data, collected data is entered into password-protected computers by data-entry clerks. Data will be backed up on another computer (also password-protected and assessable only to the data manager. Data captured in this way is, thereafter, transferred to the server/domain through the File Transfer Protocol (FTP) synchronization process of Mobenzi. The data manager at each site is responsible for uploading field data via the Internet to an off-site server. The data manager alone will have the access to the domain through a user name and password for data protection and security purpose.

All paper data files (quantitative and qualitative) are being stored in lock-and-key cabinets and the computerized data will be password-protected. Any back-ups made of the computerized data are put on separate hard drives which will also be password-protected. Only named research staff have access to the data onsite.

### Data monitoring

The trial is monitored by an independent Global Data Monitoring and Safety Board (DSMB) constituted by the National Institute of Mental Health (NIMH), the trial funders, as well as local, independent Institutional Review Boards (IRBs) at the UI and the Kwame Nkrumah University of Science and Technology, Kumasi.

The NIMH Global DSMB will ensure the safety of TPs. The board, as well as the local IRBs at the study sites, have reviewed and approved the study protocol, informed consent and all relevant documents. The other main responsibilities of the DSMB and the IRBs are, but not limited to, the following:□ Review of protocols, consent procedures, Consent Forms and safety plans prior to the initiation of the study□ Monitoring of the progress of the study, including recruitment and retention of participants, adverse events, serious adverse events (SAEs) (which will be reported as shown in Fig. 2), reasons for participant withdrawal, adherence to the timeline of the study, quality of data, and protocol violations□ Make definitive and authoritative decisions about the continuation, modification or termination of the study based on the balance of adverse events and beneficial outcomes. The data and safety monitoring plan will involve the continuous evaluation of safety, data quality and data timeliness. The PI will be expected to continuously review data and patient safety which will be reported at Trial Management Committee (TMC) and Trial Steering Committee (TSC) meetings and all discussions will be documented. The PI will also submit twice yearly progress report to the NIMH DSMB.

**Fig. 2 Fig2:**
[figure not shown]
Reporting diagram of serious adverse events (SAEs)

An independent professional trial monitoring organization is engaged by the funders to conduct random and scheduled auditing of the trial. The monitors conducted site initiation to flag off patient recruitment and have conducted three other visits to both study sites at the time of this report. Site monitoring reports are provided to the DSMB as well as to the study Institutional Review Boards.

### Sample size and potential power of the trial

The primary outcome is symptom severity as assessed with the PANSS score. Based on our previous naturalistic follow-up study of patients with psychosis undergoing treatment [37], we estimate that a mean difference of 7.5 units on the total PANSS outcome scores between the two arms will represent a clinically significant difference (given that a standard deviation of 20 was obtained for the PANSS in that study). With the target effect size of 0.38, an uninflated sample size of 112 patients per arm will be required to provide a power of 80% and at an alpha of 0.05. We expect to be able to recruit an average total of six patients per cluster. To take account of the cluster design, we inflate the estimated sample size by 1 + ((*k* − 1) × *ICC*)) where *k* is cluster size for analysis and *ICC* is the intra-cluster correlation coefficient. We estimate an *ICC* of 0.02 for the PANSS in primary care settings. Using the resulting design effect of 1.10, the inflated sample size is 246.4 (224 × 1.10). With an estimated attrition of 20% at 6 months (an estimate supported by our experience with the follow-up efforts so far) we will need to recruit a total of 296 participants. A total of 49 clusters (rounded up to 50) will be required to reach the target number of participants. We have total of 51 clusters across the two study sites and all are included in the trial.

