**Methods/design:**

COSIMPO is a single-blind, cluster randomized controlled trial (RCT) being conducted in Nigeria and Ghana to compare the effectiveness of a collaborative shared care (CSC) intervention program implemented by CAPs and primary health care providers (PHCPs) with care as usual (CAU) at improving the outcome of patients with psychosis. The study is designed to test the hypotheses that patients receiving CSC will have a better clinical outcome and experience fewer harmful treatment practices from the CAPs than patients receiving CAU at 6 months after study entry. An estimated sample of 296 participants will be recruited from across 51 clusters, with a cluster consisting of a primary care clinic and its neighboring CAP facilities. CSC is a manualized intervention package consisting of regular and scheduled visits of PHCPs to CAP facilities to assist with the management of trial participants. Assistance includes the administration of antipsychotic medications, management of comorbid physical condition, assisting the CAP to avoid harmful treatment practices, and engaging with CAPs, caregivers and participants in planning discharge and rehabilitation. The primary outcome, assessed at 6 months following trial entry, is improvement on the Positive and Negative Symptom Scale (PANSS). Secondary outcomes, assessed at 3 and 6 months, consist of levels of disability, experience of harmful treatment practices and of victimization, and levels of perceived stigma and of caregivers’ burden.

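### The 20% attrition allowance multiplies by 1.20 where it should divide by 0.80, so the target of 296 is 12 short of 308 and power is about 78.6%: a minor arithmetic correction

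*Protocol article*

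**What the plan says.** The section on sample size and potential power sets out the whole chain. The target is "a mean difference of 7.5 units on the total PANSS outcome scores between the two arms", and "a standard deviation of 20 was obtained for the PANSS in that study". The article rounds the resulting standardised effect to 0.38 and states that "an uninflated sample size of 112 patients per arm will be required to provide a power of 80% and at an alpha of 0.05". For clustering it says "We expect to be able to recruit an average total of six patients per cluster", takes an ICC of 0.02, and obtains a design effect of 1.10 and an inflated total of 246.4.

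The last step reads: "With an estimated attrition of 20% at 6 months", followed after a parenthesis by "we will need to recruit a total of 296 participants". The parenthesis says that follow-up experience so far supports the 20% estimate. The section then says that 49 clusters, rounded up to 50, are needed and that all 51 available clusters are included. The abstract repeats the total: "An estimated sample of 296 participants will be recruited from across 51 clusters".

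**The concern.** An attrition rate is a proportion of the people recruited. To have a required number left at 6 months, that number must be divided by the proportion retained. Adding 20% to the required number is a different operation and gives too small a target. The figure of 296 is exactly what the second operation gives.

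At stake is whether the stated recruitment total matches the stated 80% power under the plan's own assumptions, and whether the cluster count leaves the slack that the section implies. The total is also the headline sample size in the abstract, so readers will take it as the number that delivers 80% power.

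**Working it through.** **Inputs, all from the sample size section.** Difference 7.5; SD 20; power 80%; alpha 0.05; six patients per cluster; ICC 0.02; attrition 20%. The sidedness of alpha is not stated. Two-sided reproduces the plan's 112 per arm, while one-sided would give 88.

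**Reproducing the plan**
- Effect size: 7.5 / 20 = 0.375, printed as 0.38.
- Per arm: 2 × (1.96 + 0.8416)² / 0.375² = 111.6, so 112, and 224 in total.
- Design effect: 1 + (6 − 1) × 0.02 = 1.10.
- After clustering: 224 × 1.10 = 246.4.
- Attrition as the plan has it: 246.4 × 1.20 = 295.68, so 296. This matches. The multiplier is not written out, but division by 0.80 does not give 296.

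**Correct attrition step**
- 246.4 / (1 − 0.20) = 308, which is 12 more than 296 (4%).
- At six per cluster: 308 / 6 = 51.3 clusters, against 51 available. The plan's own count is 296 / 6 = 49.3.

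**What 296 delivers**
- Evaluable: 296 × 0.80 = 236.8, about 10 fewer than 246.4.
- Attrition that 296 can absorb: 1 − 246.4 / 296 = 16.8%.
- Effective number: 236.8 / 1.10 = 215.3, against 224.
- Power (normal approximation, as in the plan): Φ(0.375 × √(215.3 / 4) − 1.96) = 78.6%. At 308 recruits, Φ(0.375 × √(224 / 4) − 1.96) = 80.1%.
- Difference detectable with the intended power: 7.5 × √(246.4 / 236.8) = 7.65 points.

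**If all 51 clusters recruit six each**
- 51 × 6 = 306 recruited; 306 × 0.80 = 244.8 evaluable; 244.8 / 1.10 = 222.5 effective; power about 79.9%.

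**Do other readings rescue 296?**
- The section defines k as the cluster size for analysis. If six are recruited and 6 × 0.80 = 4.8 analysed, the design effect is 1 + 3.8 × 0.02 = 1.076. The need is 224 × 1.076 = 241.0 evaluable, and 241.0 / 0.80 = 301.3, so 302 recruits. Power at 296 is 79.4%. Still short, by six.
- With an effect size of exactly 0.38, the number per arm is 109. At a design effect of 1.10 the target is 218 × 1.10 / 0.80 = 299.8, so 300, with power of 79.6% at 296. Still short, by four.
- With both changes together, 218 × 1.076 / 0.80 = 293.2, and 296 would suffice. But the plan states 112 per arm and 1.10, not 109 and 1.076, so this is not its calculation.

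**The case against.** The best defence is that the slip hardly matters, and most of that defence stands.

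- **Size.** The loss is about 1.5 percentage points of power and 0.15 PANSS points in detectable difference. As the last variant above shows, that is about the size of the plan's own rounding of the effect size and choice of k.
- **296 is not a cap.** The abstract calls it an estimate, the Discussion says that all eligible and consenting participants in the randomized clusters are recruited, and all 51 clusters are in. At six per cluster the design reaches 306, two short of 308.
- **Baseline adjustment.** The Outcome analyses section adjusts continuous outcomes for their baseline value, and the sample size calculation takes no credit for it. The shortfall is a factor of 236.8 / 246.4 = 0.961. If adjustment reduces the variance by 1 − r², a baseline to 6-month correlation of about 0.20 would offset it (1 − 0.20² = 0.96). The documents give no correlation, so this is an assumption and not a demonstrated gain.

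One possible defence fails. The planned multiple imputation of missing outcomes does not by itself replace the information that the attrition allowance is meant to protect.

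In the other direction, a reader might infer that the trial is materially underpowered, perhaps by adding a small-sample t reference with cluster-based degrees of freedom or a penalty for unequal cluster sizes. The documents do not support that as a consequence of this error. A t reference is a change of method that lowers power at 308 as well. The article classes clusters as small or large by beds but gives no distribution of recruits per cluster, so any penalty would rest on an assumed figure. It is also a separate question, of a kind that a condensed article may leave to the full protocol.

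**Conclusion.** The recruitment total is wrong as written, and the correction is minor. Under the plan's own 112 per arm, design effect of 1.10 and 20% attrition, the target is 308 and not 296. At 296, about 237 patients are evaluable and power for 7.5 points is about 78.6%. No reading that keeps the stated 112 per arm makes 296 correct.

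These figures assume a two-sided alpha of 0.05, the normal approximation that reproduces the plan's 112, equal cluster sizes as in the plan's formula, and no precision gain from baseline adjustment. The finding does not show that the trial cannot answer its primary question, and it calls for no change to the design, the allocation or the analysis.

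**What to change.** Choose one of two corrections to the sample size section.

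1. **Correct the target.** Replace the last step with 246.4 / (1 − 0.20) = 308 and revise the cluster statement: 308 needs 51.3 clusters at six each, against 51 available. Say that 51 clusters at six each yield 306 recruits and about 79.9% power, or that a little over six per cluster is needed (308 / 51 = 6.04).
2. **Keep 296 and restate what it delivers.** For example: 296 recruited, about 237 evaluable at 20% attrition, about 78.6% power for a difference of 7.5 points.

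Under either option, make the abstract agree. It would be fair to add that the primary analysis adjusts for baseline, that the calculation takes no credit for this, and that it may offset the small shortfall.

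The second option costs only a change of wording and a slightly lower stated power. The first adds at most 12 recruits to the target in clusters that are already included.

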### Data analyses

Initial analyses will include comparisons of baseline characteristics of individuals who consented and did not consent, and participants who could and could not complete baseline assessments, and of the distribution of potential confounding factors. Findings will be reported as per Consolidated Standards of Reporting Trials (CONSORT) guidelines for cluster randomized controlled trials [38] including a trial flow chart (see Fig. 3). This will include the flow of clusters and participants through each stage of the trial, including the number eligible, randomly assigned, receiving the intended treatment, completing the study protocol and analyzed for the primary outcome.

**Fig. 3 Fig3:**
[figure not shown]
COllaborative Shared care to IMprove Psychosis Outcome (COSIMPO) trial flow chart

The outcome measures will be summarized at baseline, 3-month and 6-month follow-ups by intervention arm and overall. These will be summarized by means (SD), medians (IQR) or numbers and proportions as appropriate (and including age, gender, baseline outcome score), adjusting for cluster. For continuous outcomes, histograms within each arm will be plotted in order to assess how closely the scales follow a normal distribution to determine how to describe the outcomes and how to properly do the inferential analysis. The clusters will be described in terms of gender, education, country site, and profile of the CAP.

### Outcome analyses

The primary analyses will be intention-to-treat at the 6-month follow-up visit adjusted for baseline measures. That is, after randomization, patients will be analyzed according to their allocated treatment irrespective of the treatment that they actually received. These analyses will also disregard adherence to the intervention or withdrawal from the trial. Random-effects logistic regression will be used to analyze binary outcomes, adjusting for country site and cluster size as random-effects variables. Analyses of continuous outcomes will use random-effects linear regression, additionally adjusting for the baseline value of that outcome. Adjustments will also be made for any a-priori-defined sets of potential confounding variables for which randomization did not achieve balance between the two arms at baseline. This may include, for example, differences in the type of CAPs (e.g., traditional healers versus faith healers). Effect sizes will be reported as: (1) crude and adjusted relative risks (ARRs) estimated using the marginal standardization technique with 95% confidence intervals for the ratios estimated via the delta method [46] for binary outcomes and (2) as mean differences and standardized mean differences (SMDs), with 95% confidence intervals for continuous outcomes. Missing data on the outcomes will be estimated using multiple imputations in Stata. Secondary analyses will include repeated measures analyses of data collected at 3 and 6 months, which make efficient use of all available data. No interim analysis of outcomes is planned.

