## Method/design

The study is a single-blind, cluster randomized controlled trial (RCT) being conducted in Nigeria and Ghana. The sampling frame consists of all the clusters in the 11 local government areas (LGAs) in and around the city of Ibadan in Nigeria and Ashanti region in Ghana. A cluster is composed of a primary health care clinic (PHC) and all the CAP facilities in its neighborhood, defined as the catchment area typically served by the PHC. That is, a cluster has one PHC and its neighboring CAP facilities, the number of the latter being determined by distance, ease of contact, and administrative considerations. Clusters were composed such that the CAP facilities are readily accessible to the PHCW in order to facilitate clinical engagement and support. All CAP facilities in the two study sites, previously identified and mapped during the formative stage of the project, were allocated to clusters. A total of 51 clusters were composed. Randomization of clusters was carried out before recruitment of trial participants (TPs). Allocation of clusters to each of the study arms was conducted by a statistician at the University of Ibadan (UI) Department of Epidemiology and Statistics with no other involvement in the day-to-day implementation of the study. Allocation to the two arms was balanced by site (Ghana versus Nigeria) and by size of the cluster, using the number of beds in each cluster (small versus large). Patients who are invited will not be informed of their allocation until their eligibility has been established and they have consented to participate. Fifty-one clusters were randomized into the two arms of the study across the two study sites.

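### The outcome models name country and cluster size as random effects but not the randomised cluster, so as written they ignore within-cluster correlation

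*Protocol article*

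**What the plan says.** The Method/design section sets out the design. "Fifty-one clusters were randomized into the two arms of the study across the two study sites", and "a cluster has one PHC and its neighboring CAP facilities". "Allocation to the two arms was balanced by site (Ghana versus Nigeria) and by size of the cluster", with size split into small and large by number of beds. Country and size are therefore two-level balancing factors, and the cluster is the unit of randomisation.

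The sample size section treats outcomes within a cluster as correlated: "To take account of the cluster design, we inflate the estimated sample size". It uses an ICC of 0.02 and six patients per cluster, giving a design effect of 1.10.

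The Outcome analyses section specifies random-effects logistic regression for binary outcomes, "adjusting for country site and cluster size as random-effects variables". The next sentence reads "Analyses of continuous outcomes will use random-effects linear regression, additionally adjusting for the baseline value of that outcome". The section mentions no random intercept for cluster, cluster-robust variance, GEE or cluster-level analysis.

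The one reference to adjusting for cluster comes after Fig. 3, under Data analyses. It concerns descriptive summaries: "numbers and proportions as appropriate (and including age, gender, baseline outcome score), adjusting for cluster".

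**The concern.** In a cluster randomised trial, the variance of the arm comparison includes the variation between clusters. A model respects the randomisation only if it represents that variation. The protocol lists its random effects, and the list contains the balancing factors in place of the randomised unit.

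This causes two problems. First, a variance component cannot be usefully estimated from two levels, so country and size are poor candidates for random effects. Second, because the arms are balanced within country and size, differences between countries or size groups largely cancel from the arm contrast. What remains is variation between clusters in the same stratum, and neither named term absorbs it. Patients in one cluster would be treated as independent given country and size.

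Confidence intervals would be too narrow and p-values too small for the PANSS outcome and for any secondary outcome that is correlated within cluster. The analysis would also leave out the correlation that the sample size was enlarged to allow for.

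**Working it through.** **Inputs from the protocol.** Difference 7.5, SD 20, power 80%, alpha 0.05 (taken as two-sided), six patients per cluster, ICC 0.02, attrition 20%, total 296, 51 clusters.

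**The plan's own figures.** The two-sample formula gives 112 per arm, or 224. Design effect = 1 + (6 − 1) × 0.02 = 1.10. Then 224 × 1.10 = 246.4 and 246.4 × 1.20 = 295.7, which rounds to 296. The stated figures reproduce, so the planning does carry within-cluster correlation.

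**Analysed patients per cluster.** 296 × 0.80 = 236.8 evaluable, and 236.8 / 51 = 4.64.

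**Effect of omitting the cluster term.** With k patients per cluster, DE = 1 + (k − 1) × ICC. The true standard error is √DE times the one the model reports. The actual two-sided type I error of a nominal 5% test is 2 × (1 − Φ(1.96 / √DE)).

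At ICC 0.02 and k = 4.64, DE = 1 + 3.64 × 0.02 = 1.073 and √DE = 1.036. The model's standard error is about 3.5% too small, and the error rate is 2 × (1 − Φ(1.96 / 1.036)) = 5.9%.

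For unequal cluster sizes, DE = 1 + ((1 + CV²)k − 1) × ICC. With CV 0.7 this is 1 + (1.49 × 4.64 − 1) × ICC = 1 + 5.92 × ICC.

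| ICC | k = 4.64, equal | k = 6, equal | k = 4.64, CV 0.7 |
|---|---|---|---|
| 0.02 (protocol) | 5.9% | 6.2% | 6.4% |
| 0.05 (assumed) | 7.1% | 8.0% | 8.5% |
| 0.10 (assumed) | 9.3% | 11.0% | 12.0% |

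The CV of 0.7 is also an assumption; the protocol gives none.

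**Simulation checks.** Both checks used 51 clusters and no cluster term, with country and size entered as fixed covariates in place of the two random effects.
- Equal clusters of five, 20,000 runs per ICC: rejection rates under the null were 5.1%, 6.0%, 7.5% and 9.6% at ICC 0, 0.02, 0.05 and 0.10.
- Unequal clusters, 4,000 runs: 6.5%, 8.7% and 11.3% at ICC 0.02, 0.05 and 0.10.
- In the equal-cluster simulation, a cluster-level analysis adjusted for country and size gave 4.8% to 5.1% at every ICC.

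**On the PANSS scale at ICC 0.02.** Ignoring baseline adjustment, SE = 20 × √(2 / 118.4) = 2.60, so the 95% half-width is 1.96 × 2.60 = 5.1 points without the cluster term. With it, the half-width is 5.1 × 1.036 = 5.3 points.

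**The case against.** The strongest reply is that the wording is loose rather than the analysis wrong. In a cluster trial, random-effects regression ordinarily means a random intercept for cluster. The protocol inflates its sample for the ICC and commits to CONSORT reporting for cluster trials, so the authors plainly knew about clustering. The fitted model may well have the right term, and an analysis plan that is not at hand may say so. This is fair on intent. However, the article does not leave the random effects to another document: it names them, and the cluster is not among them. If a cluster intercept was meant, the sentence still misstates the model.

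Second, the sentence listing the random effects concerns binary outcomes, and the PANSS sentence lists none. That is correct. The extension to PANSS rests on the word for additional adjustment, which makes the linear model an add-on to the one just described. This is the natural reading, but it is an inference.

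Third, size is two-level in the allocation, and the analysis section does not say how it enters the model. That also stands. Even so, a term for size in any form is not a term for the cluster.

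Fourth, the consequence is small on the protocol's own figures: about 0.2 PANSS points in half-width against a 7.5-point target. If country or size explained part of the planned ICC, the residual effect would be smaller still. This holds for PANSS at ICC 0.02. It gives no assurance for the secondary outcomes, for which the protocol states no ICC. Harmful practices are described as part of usual care for some healers, so patients of one facility may share that exposure. A larger ICC there is plausible, though not documented.

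**Conclusion.** The concern holds. As written, the outcome models put random effects on the balancing factors and leave out the unit that was randomised. The sample size assumes a correlation that the analysis does not carry.

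At the protocol's ICC the inflation is modest: about 5.9% against a nominal 5% with 4.64 analysed patients per cluster, or 6.2% with six. The range up to 12.0% rests on assumed ICCs of 0.05 to 0.10 and an assumed cluster-size CV of 0.7. All these figures take the text literally and treat the stated ICC as correlation remaining within country-by-size strata.

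The case for correction does not depend on the larger figures. This is the confirmatory model for the primary outcome and the stated model for the secondary ones, and it does not respect the randomisation. It should be corrected before outcome data are analysed.

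**What to change.** Replace the description of the random effects with wording such as: *All outcome models include a random intercept for cluster (the primary care clinic and its healer facilities, 51 levels) and fixed effects for trial arm, country and bed-size stratum. Models for continuous outcomes also include the baseline value of the outcome.*

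Use the same cluster term in the logistic models, and derive the marginal-standardisation relative risks and their delta-method intervals from those models. With about 25 clusters per arm, a small-sample correction (Kenward-Roger or Satterthwaite) is advisable for the continuous outcomes. That detail can sit in the analysis plan.

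When listing the randomisation factors, the sponsor should reconcile two accounts. Method/design gives country site and cluster size, whereas the Discussion says clusters were stratified by local government area and size. The fixed effects should match what was done.

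The cost is one sentence and no new data. Intervals become slightly wider, by about 3.6% at the planning ICC (√1.073 = 1.036).

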### Secondary hypotheses

Using outcome data collected at 3 and 6 months following trial entry, we will test the following secondary hypotheses:Persons with psychotic experience treated by CAPs in the collaborative care program will be less likely to receive harmful treatment or be subject to human rights abuses (such as chaining, beating, starving, exposure to natural elements, scarification, isolation, fasting) than those in the care as usualParticipants in the intervention arm will be less likely to experience victimization and abuse from their caregivers. Victimization is defined as an act or action that exploits or treats a patient unfairlyParticipants in the intervention arm will have significantly less disability in the areas of psychological, occupational and social functioning as measured with the World Health Organization’s Disability Assessment Scale (WHO-DAS) than those in the control arm

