### Assessment instruments

The psychosis section of the Structured Clinical Interview for DSM-IV Axis 1 disorders (SCID) is used to confirm the diagnosis of psychosis. The SCID is a semi-structured interview for making the major DSM-IV Axis 1 diagnosis. Information collected by trained RAs using the SCID is reviewed by research psychiatrists to assign subtype diagnosis of psychosis and make a rating on course of the psychosis illness. The Positive and Negative Syndrome Scale (PANSS) [28] is used to measure symptom severity of psychosis at baseline, 3 and 6 months. Disability is being measured with the World Health Organization’s Disability Assessment Schedule 2.0, a generic tool for assessing health and disability [31]. The Proxy version of WHO-DAS is used when a TP is unable to provide reliable information. The 29-item Internalized Stigma of Mental Illness (ISMI) scale [32] is used to assess level of self-stigma. The burden of caring for TPs by their caregivers is being assessed with the Family Burden Interview Schedule (FBIS) [33], a standardized instrument designed for the. The Life Chart Schedule (LCS) is being used to assess the long-term course of the psychotic illness in four key domains (symptoms, treatment, residence and work) [34]. To capture the range of services and the cost associate with their use, we use the Service Utilization Questionnaire [35] (adapted for COSIMPO). The SUQ systematically collects resource-use data, including cost of care received from CAPs, consultations with PHCPs and with other conventional health providers, use of herbs and drugs, cost of treatment, including those of rituals and sacrifices, and any other service use-related costs. Checklists of harmful treatment practices, human rights’ abuses and of victimization, developed with information obtained during the formative stages of the Partnership for Mental Health Development in sub-Saharan Africa (PaM-D), are used for the indicated purposes. These assessments are conducted through both observation during visits by the RAs to CAPs facilities and by patient interviews. For example, respondents are asked if they have experienced any of the practices or abuses in a defined period of time (at the baseline, this will be in the previous 3 months, and at follow-up assessments, this will be “since the last time we spoke with you”). Every positive answer is followed by exploration of the number of times that the event had been experienced or the duration of its occurrence, whichever is relevant to the event.

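### The outcome-analysis section promises baseline adjustment in general but gives the baseline value only to continuous outcomes, so the logistic model for harmful practices, abuses and victimization omits a baseline value that the trial collects

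*Protocol article*

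**What the plan says.** Three statements in the Outcome analyses section of the protocol article bear on this point.

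- The general rule: "The primary analyses will be intention-to-treat at the 6-month follow-up visit adjusted for baseline measures".
- The binary model: "Random-effects logistic regression will be used to analyze binary outcomes, adjusting for country site and cluster size as random-effects variables".
- The continuous model: "Analyses of continuous outcomes will use random-effects linear regression, additionally adjusting for the baseline value of that outcome".

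A further clause concerns imbalance seen at baseline: "Adjustments will also be made for any a-priori-defined sets of potential confounding variables for which randomization did not achieve balance between the two arms at" (the quote stops one word short of the end of the sentence). Its example is type of healer. Effects on binary outcomes are to be reported as crude and adjusted relative risks by marginal standardization.

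Under Secondary hypotheses, participants in the collaborative arm "will be less likely to receive harmful treatment or be subject to human rights abuses", and victimization by caregivers is worded in the same way. The abstract puts harm beside clinical outcome, saying that patients in the collaborative arm "will have a better clinical outcome and experience fewer harmful treatment practices from the CAPs than patients receiving CAU". Under Assessment instruments, the checklists for harmful practices, abuses and victimization have a baseline recall window: "at the baseline, this will be in the previous 3 months".

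**The concern.** The general rule and the model sentences do not say the same thing. If the general rule covers every outcome, the continuous sentence has no reason to introduce the baseline value as an extra term. If the model sentences govern, the logistic model has no baseline outcome, and an analyst who follows them will leave it out.

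Precision on the harm and victimization hypotheses is at stake. The section on responses to harmful practices says that such practices are often part of some healers' standard care. If so, exposure may differ between facilities and persist within them, and a participant's baseline checklist value could predict the follow-up value well. Leaving out a strong predictor that has already been collected gives away power. The allocation factors in the Method/design section, site and number of beds, do not measure how harmful a facility's practices are.

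**Working it through.** **1. The plan's own figures.** The sample size section uses a difference of 7.5, SD 20, 80% power and alpha 0.05. Then 2 × (1.960 + 0.842)² × 20² / 7.5² = 111.7, that is 112 per arm, as stated. The design effect is 1 + (6 − 1) × 0.02 = 1.10, and 224 × 1.10 = 246.4, as stated. The total of 296 is 246.4 × 1.2, rounded. All of this concerns PANSS. No rate, effect, intra-cluster correlation or power is given for any binary outcome, so what follows rests on assumptions.

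**2. Rough guide.** Suppose a test has 80% power unadjusted and the covariate removes a share rho² of the variance. Power becomes Φ((1.960 + 0.842)/√(1 − rho²) − 1.960).

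- rho 0.2: 81.6%
- rho 0.3: 83.6%
- rho 0.4: 86.4%
- rho 0.5: 89.9%

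This is a linear-model approximation and ignores clustering.

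**3. Simulation allowing for clustering.** There were 51 clusters of 5 analysed patients (255; the plan implies 296 × 0.8 = 237) and 600 runs per setting. Assumed risks were 50% in control and 32% to 33% in intervention. Baseline and follow-up shared cluster and person effects, with SDs on the log-odds scale. The model was logistic with cluster-robust standard errors and a t reference on 49 df, standing in for the random-effects model and without site or size terms.

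| Cluster SD / person SD | Baseline–follow-up correlation (phi) | Power without baseline | Power with baseline | Gain (points) |
|---|---|---|---|---|
| 0.26 / 0 | 0.02 | 78.2% | 77.5% | −0.7 |
| 0.26 / 1 | 0.18 | 79.3% | 81.5% | 2.2 |
| 1 / 0.5 | 0.20 | 57.5% | 66.5% | 9.0 |
| 1 / 1.5 | 0.35 | 62.5% | 76.8% | 14.3 |
| 1.5 / 1.5 | 0.42 | 51.7% | 74.8% | 23.1 |

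The Monte Carlo standard error of a single power is at most √(0.25/600) = 2.0 points. With no true effect, the rejection rate was 3.8% to 5.8% across both models.

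A second simulation (GEE logistic, about 237 analysed, control risk 50%, other effect sizes) points the same way: 69% to 73% at correlation 0.13, 71% to 79% at 0.27, 76% to 88% at 0.36 and 78% to 93% at 0.43.

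**4. Chance difference at baseline.** Take 296 patients and an assumed 50% baseline prevalence. The standard error of the arm difference is √(2 × 0.25 × DE/148), with DE = 1 + (296/51 − 1) × ICC. At ICC 0.02, DE = 1.096, SE = 0.061 and the 95% range is ±12 points. At ICC 0.20, DE = 1.961, SE = 0.081 and the range is ±16 points. The standard error of the unadjusted test already allows for such differences. Adjustment recovers precision and does not repair a bias.

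**5. If baseline harm already reflects allocation.** Assume 51 clusters of 5, cluster and person SD 1.0, GEE logistic and 400 runs per setting. With half of the log-odds effect already present at baseline, adjustment moves the standardized relative risk from 0.67 to 0.71 and power from 58% to 57%. With three-quarters present, they move from 0.68 to 0.73 and from 58% to 50%.

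**The case against.** The strongest reply is that no omission is established: the opening sentence promises baseline adjustment without limiting it to continuous outcomes, and a condensed article may leave full covariate lists to another document. That stands against calling the omission unequivocal. It does not remove the point, because the article does state a covariate set for the binary model and that set conflicts with the broad reading of the opening sentence.

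Secondly, harm might not be analysed as binary. The abstract speaks of fewer practices, and the checklist explores number of times or duration. A count analysed as continuous would already get its baseline value. The wording of the secondary hypotheses nonetheless points to the logistic model.

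Thirdly, baseline may predict weakly. Patients are approached on consecutive admission, so a 3-month recall may reach back before admission; by follow-up they may have left the facility; and victimization is by caregivers. This stands, and it is why the lower end of the range is about nil.

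Fourthly, adjustment is not free of risk. Clusters were randomized before recruitment and providers trained before the trial began. Primary care providers in the collaborative arm make weekly visits, enrolment runs for about nine months, and baseline assessors are not blind. Part of a later recruit's recall window may follow the start of the intervention at that facility, and adjustment could then attenuate the effect. This is a real, if small, downside and shapes the fix.

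**Conclusion.** The section is inconsistent and, read by its model sentences, the logistic model leaves out a baseline value that is collected. The point concerns consistency and efficiency for secondary hypotheses, one of which is also named in the abstract.

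Under the assumed rates, cluster variances and correlations, the gain from adjusting is about nil when cluster variance is small and the correlation weak (−0.7 to 2.2 points). It is 9 to 23 points when cluster variance is large and phi lies between 0.20 and 0.42. The documents do not show which case applies.

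A reader might infer that the unadjusted test is biased or has inflated type I error. The documents do not support that: allocation was randomized, and the simulated rejection rate stayed near 5% without the baseline value. A reader might also infer that few clusters leave the comparison badly exposed to imbalance. There are 51 clusters, balanced by site and size, and the imbalance clause offers some protection, although it depends on the observed data and does not name baseline harm.

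**What to change.** Amend the Outcome analyses section so that the general rule and the model sentences agree:

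- State that binary outcomes, like continuous ones, are adjusted for the pre-specified baseline value of that outcome. For harmful practices, abuses and victimization, this is the participant's baseline checklist value, with its form (any versus none, or number of types) fixed in advance.
- State that the adjusted relative risk is standardized over that value.
- Report the relative risk without the baseline value beside it as a sensitivity analysis, giving the reason: for later recruits the baseline value may already reflect allocation.

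The cost is a sentence or two and one extra covariate. The data are already collected, missing baseline checklists can be added to the multiple imputation already planned for outcomes, and crude and adjusted relative risks are already to be reported. The downside is possible attenuation of the adjusted estimate, which the companion estimate would help to reveal.
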